### 5.2 Statistical analysis

Baseline data (gender, age, vital signs) will be descriptively summarized. Differences of measurement data between the groups will be assessed using *t*-test for normally distributed continuous variables and Wilcoxon signed rank test for non-normally distributed variables.

Measurement data of different groups in each visit will be reported as mean ± standard deviation (SD). Intra-group comparisons between baseline and each visit will be conducted by using paired *t*-test (or Wilcoxon signed rank test). Comparisons between groups will be conducted by using an analysis of variance (ANOVA), with other confounding factors like multicenter character conducting the covariate analysis. Statistical analysis for the data which do not meet above conditions (e.g., non-normal) will be conducted with the use of non-parametric test.

For AEs analysis, comparisons of the incidence rate of AEs between groups will be conducted with the use of χ^2^ test. The investigators need to list and describe the AEs occurred in this trial. If the data do not conform to χ^2^ test (data include 0, or theoretical frequency is below 5), Fisher’s exact test will be used.

For laboratory parameters, Spearman’s coefficient correlation will be used for comparison with different parameters and one way ANOVA test for significant correlation between groups.

All *p* values and 95% confidence intervals are two-sided, and *p* < 0.05 is considered statistically significant. Statistical analyses will be carried out exclusively by an independent statistician. All analyses will be performed by using SPSS, version 24 (SPSS).

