#### 2.4.2 Baseline randomization visit

Eligible subjects will have medical consultation and assessment by Registered Chinese medicine practitioner (CMP) investigators with at least 3 years’ clinical experience. Vital sign will be assessed, medical history and concomitant medications will also be recorded at baseline. TNSS, Rhinoconjunctivitis Quality of Life Questionnaire (RQLQ) score for aged 13 and above and Paediatric Allergic Disease Quality of Life Questionnaire (PADQLQ) score for aged 12 and Visual Analog Scale (VAS) for frequency and severity of AR episodes will be evaluated. Blood samples for serum cytokines (IL-10 and IL-17) will also be collected. Subjects will be randomly assigned (in a 1:1 ratio) to receive for 8 weeks of either “Yupingfeng Powder with variation” granules or placebo granules.

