### 2.5 Randomization and blinding

The eligible subjects will be randomly assigned to either experimental group or control group at the ratio of 1:1. A randomization schedule will be generated by computer to assign subjects to the treatment sequences. Concealment of allocation will be ascertained by an independent research staff, and identically designed treatment packs will be used for study drugs.

This is a double-blind randomized controlled trial. All study investigators and subjects will be blinded in the study. The random allocations will be put into opaque envelops with sequential study numbers. Two sets of the envelope will be prepared, with one set for randomization at the site, and another set for storage in the investigator’s office for emergency un-blinding.

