## 3 Study outcomes

### 3.1 Primary outcomes

1. The change in the TNSS at week 8.

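### Section 5.2 names a paired test, the Wilcoxon signed rank test, for between-group differences in non-normal data, although the two arms are independent

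*Protocol article*

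**What the plan says.** Section 5.2 (Statistical analysis) of the protocol article makes four statements that bear on this point.

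- Its first paragraph opens with a descriptive summary of baseline data and continues: "Differences of measurement data between the groups will be assessed using" a t-test for normal data. The alternative is given in the same sentence: "continuous variables and Wilcoxon signed rank test for non-normally distributed variables".
- The second paragraph turns to data at each visit. For change within an arm it says "Intra-group comparisons between baseline and each visit will be conducted by using paired" t-test, with the signed rank test as the alternative.
- The same paragraph then gives a between-group rule: "Comparisons between groups will be conducted by using an analysis of variance (ANOVA"), with covariate analysis for confounders.
- It closes with a second fallback for data that do not meet these conditions: "e.g., non-normal) will be conducted with the use of non-parametric test". No test is named.

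On the design, Section 2.5 says "The eligible subjects will be randomly assigned to either experimental group or control group at the ratio of 1:1", and Section 2.4.2 says the same ("Subjects will be randomly assigned (in a 1:1 ratio"). Neither describes matching or crossover. The primary outcome in Section 3.1 is "The change in the TNSS at week 8".

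**The concern.** The signed rank test works on differences within pairs. It fits the within-group comparison, where each person has a baseline and a visit value. It does not fit a comparison of active with placebo, where no value in one arm belongs with any particular value in the other. Section 5.2 gives this one paired test to both kinds of comparison, and the test for independent samples, the Wilcoxon rank-sum (Mann-Whitney) test, appears nowhere in the article.

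This is a test named wrongly, not a detail left to a later analysis plan. An analyst who followed the sentence would have to invent pairs, and the reported p-value would then depend on how they were formed. An analyst who noticed the problem would have to choose another test, possibly with the data already in view.

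**Working it through.** The article attaches no figure to this choice of test, so there is none to reproduce. The check sets test against design and then looks at what happens if the sentence is followed.

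**1. Test against design**

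| Comparison in Section 5.2 | Structure of the data | Test named for non-normal data | Fits? |
|---|---|---|---|
| Between groups, first paragraph | Independent arms, 1:1 | Signed rank | No |
| Within group, baseline to visit | Two values per person | Signed rank | Yes |
| Between groups, second paragraph | Independent arms, 1:1 | Unnamed non-parametric | Undefined |

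**2. Unequal arms**

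Inputs from Section 5.1: 52 evaluable participants, 10% dropout, 58 randomised, 29 per arm. The dropout step is 52 / 0.9 = 57.8, so 58, which allows 58 − 52 = 6 losses.

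Assume exactly 29 per arm at the start and exactly 6 losses unrelated to arm. The arms then stay equal only if 3 are lost from each:

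C(29,3)² / C(58,6) = 3,654² / 40,475,358 = 0.33

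On these assumptions unequal arms occur about two times in three. A trial run of the signed rank test with 27 against 25 values returned an error. Only 25 pairs can be formed, so 2 people would have to be dropped.

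**3. Equal arms: dependence on the pairing**

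The article gives no usable distribution, so these inputs are assumptions: 26 per arm (52 / 2); scores drawn from normal distributions with means 4.5 and 6.0 and SD 2.5, rounded and held within 0 to 12. The upper limit is 4 items × 3 points from Section 3.3.1, if the items are summed. One data set was drawn and one arm re-ordered at random 5,000 times.

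| Test on the same data | p-value |
|---|---|
| Rank-sum | 0.024, a single value |
| Signed rank, minimum to maximum | 0.0005 to 0.118 |
| Signed rank, 5th to 95th percentile | 0.006 to 0.052 |
| Signed rank, median | 0.021 |

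The share of pairings with p < 0.05 was 0.944, so about 6% were not significant (1 − 0.944 = 0.056).

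The effect on the decision varies with the data. In a second assumed example (change-score means −3.5 and −1.5, SD 2.5, 26 per arm), p ran from 0.0002 to 0.044 over 5,000 pairings against a rank-sum p of 0.007. There the p-value moved but every pairing stayed below 0.05.

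**4. Error rate and power under random pairing**

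Assumed log-normal data, log-scale SD 0.8, 26 per arm, 5,000 simulated trials per row. The shift is 0.8 × 0.8 = 0.64 on the log scale.

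| Scenario | Signed rank | Rank-sum |
|---|---|---|
| No difference (type I error) | 0.050 | 0.045 |
| Shift of 0.64 (power) | 0.736 | 0.787 |

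The simulation error at 0.05 is √(0.05 × 0.95 / 5,000) = 0.003, so neither error rate departs clearly from 5%. This is expected: if pairs are formed without regard to the data and the arms share one distribution, the paired differences are symmetric about zero. The power loss is 0.787 − 0.736 = 0.051, about 5 percentage points.

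**The case against.** The strongest reply concerns reach. The signed rank sentence directly follows the one on baseline data and may be meant mainly for baseline comparisons. The next paragraph, on visit data, has its own between-group rule (ANOVA with covariates) and its own fallback, which a rank-sum test would satisfy. A reader might infer that the primary week-8 TNSS p-value will rest on arbitrary pairs; the text does not establish that. The reply does not remove the error. The sentence speaks of measurement data between the groups, the later fallback neither names a test nor withdraws the earlier one, and a paired test is wrong for independent groups even at baseline.

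A reader might also infer inflated false positives. The check shows none under random pairing. That protection would not cover pairs chosen with the results in view, but nothing in the article suggests such a choice.

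A third tempting inference is that IgE and cytokines will be skewed and so trigger this rule. The article does not describe their distributions, and it has a separate sentence on laboratory parameters with one-way ANOVA. Table 1 lists IgE and cytokines under outcome rather than laboratory assessment, so which sentence covers them is itself unclear. No criterion for non-normality is given either, so how often the fallback would apply is unknown.

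Finally, the wording is probably a slip for rank sum, and an independent statistician would often notice it, since the test fails on unequal arms. That lowers the practical risk, but the written rule still needs correcting.

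**Conclusion.** The error is certain on the text: a paired test is named for differences between two independent, unpaired arms. The consequences are moderate. If the sentence is followed, the test cannot be computed with unequal arms without dropping people. With equal arms the p-value is arbitrary (0.0005 to 0.118 in one example) and some power is lost (about 5 percentage points in one scenario). The type I error was not inflated under random pairing. All the simulated sizes rest on assumed data, and the pairing ranges come from single data sets.

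The documents do not settle whether the primary comparison is affected, because Section 5.2 holds two between-group statements that are not reconciled. The point should be fixed, but it does not by itself put the primary analysis in doubt.

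**What to change.** In Section 5.2:

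- In the first paragraph, replace the signed rank test with the Wilcoxon rank-sum (Mann-Whitney) test for between-group comparisons of non-normal data.
- In the second paragraph, name the same test where only a non-parametric test is mentioned, so that the two between-group statements agree.
- Keep the signed rank test only for within-group comparisons of baseline with each visit.
- Optionally, report a Hodges-Lehmann difference with its 95% confidence interval beside the rank-sum test. This is good practice but is not needed to correct the error.

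The cost is a sentence or two. The rank-sum test is available in the named software, and neither data collection nor sample size changes.

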#### 2.2.1 Inclusion criteria

• Aged 5 or above;• Subjects with deficiency of lung and spleen Qi, which will be determined by Chinese Medicine Practitioners (CMP). (There will be a checklist of 13 TCM symptoms, subjects with two or more of the symptoms will be determined as deficiency of lung and spleen Qi);• At least two or more allergic symptoms (rhinorrhea, sneezing, nasal obstruction and nasal itching) for a cumulative period greater than 1 h per day. These symptoms may be accompanied by itchy and red eyes and tears; and• Able to provide voluntary written informed consent.

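### Section 5.2 plans paired significance tests within each arm at every visit and does not tie the primary outcome to the between-arm contrast, leaving room for a misleading statement of significant improvement

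*Protocol article*

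**What the plan says.** Section 5.2 of the protocol article makes three statements that matter here.

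- On change within an arm: "Intra-group comparisons between baseline and each visit will be conducted" with paired t-tests, or the Wilcoxon signed rank test. The sentence covers every visit and is not limited to TNSS.
- On the arms against each other, in the next sentence: "Comparisons between groups will be conducted by using an analysis of variance (ANOVA"), with covariates. An earlier sentence also names a t-test for differences between groups.
- On significance: all p values are two-sided, and p "< 0.05 is considered statistically significant". No class of test is exempted.

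Section 3.1 gives the primary outcome in full as "The change in the TNSS at week 8". It does not say whether this is a difference between arms or a change within one. In 5.2 the only test expressly framed as a comparison with baseline is the within-arm one. The same section describes the baseline data summary as descriptive but does not use that label for the within-arm tests.

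**The concern.** The trial is randomised and placebo-controlled, and the Abstract sets out to show better efficacy than placebo granules. Only a comparison of the arms can answer that. A paired test asks whether one arm's mean moved from its own baseline, and it cannot separate the drug from whatever else moved the scores.

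Other influences are plausible here. Section 2.2.1 admits people who currently have symptoms: "At least two or more allergic symptoms (rhinorrhea, sneezing, nasal obstruction and nasal itching) for a cumulative period greater than 1 h per day". The Introduction links the occurrence of allergic rhinitis to living habits and environment. Section 3.3.1 has subjects rate TNSS themselves. Scores could therefore fall in both arms with no drug effect.

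What is at stake is the wording of the results. If the between-arm comparison is inconclusive, a small within-arm p value invites a statement of significant improvement. A significant result in the active arm beside a non-significant one in the placebo arm is easily misread as a difference between arms, which it does not show.

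**Working it through.** **Inputs from the article**

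- Evaluable subjects: 52, so 52 / 2 = 26 per arm (5.1, with 1:1 allocation in 2.5). The dropout step reproduces: 52 / 0.9 = 57.8, rounded up to 58. Whether 52 follows from the means and SDs quoted in 5.1 is a separate question; 26 is used here only as the stated arm size.
- Threshold: 0.05 two-sided (5.2).
- Post-baseline TNSS visits: weeks 4, 8, 12 and 16 (Table 1).

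**Input not in the article**

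- The change from baseline shared by both arms when the drug has no effect. It is written e, in units of the SD of the change score, and ranged from 0.2 to 0.75. For example, a 1.0-point change with an SD of 2.5 gives e = 0.4, and 1.5 points with an SD of 2.0 gives e = 0.75.

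**Number of tests.** TNSS alone gives 2 arms × 4 visits = 8 within-arm tests. Counting one VAS score and one quality-of-life score at four visits each, and IgE, IL-10 and IL-17 at two visits each, the total is 2 × (4 + 4 + 4 + 2 + 2 + 2) = 36.

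**Chance that one arm's paired test is significant.** With n = 26 there are 25 degrees of freedom and the critical value is t = 2.06. The noncentrality parameter is e × √26. Let p be the probability that |t| exceeds 2.06. At e = 0.4, the noncentrality is 0.4 × 5.099 = 2.04 and p = 0.50.

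**Chance that the active arm alone is significant.** The arms are independent and share the same e, so this is p × (1 − p). At e = 0.4 it is 0.50 × 0.50 = 0.25.

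| Shared change e (SD) | One given arm significant, p | Active significant, placebo not, p(1 − p) |
|---|---|---|
| 0.2 | 17% | 14% |
| 0.3 | 31% | 21% |
| 0.4 | 50% | 25% |
| 0.5 | 69% | 21% |
| 0.6 | 84% | 14% |
| 0.75 | 96% | 4% |

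The product p(1 − p) cannot exceed 25%. It falls at the upper end because both arms then tend to be significant together.

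**Comparator.** With no treatment effect, a two-sided 5% between-arm test is wrong in the drug's favour in 5% / 2 = 2.5% of trials, whatever the shared change. A simulation (20,000 runs, 26 per arm) put its two-sided error at 4.8% to 5.2% for shared changes from 0 to 0.8 SD.

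**Repeated visits.** In the same simulation, with the shared change equal at all four visits and an assumed correlation of 0.5 between visits, the active arm was significant at one or more visits in 62% of trials at e = 0.3 and 93% at e = 0.5.

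**The case against.** The case on the other side is substantial.

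- **A between-arm analysis is planned.** The ANOVA follows directly in 5.2, the sample size in 5.1 compares two group means, and the Abstract's aim is superiority to placebo. A reader might infer that efficacy will be judged from the paired tests, or that the primary analysis is invalid. No part of the article says so. This stands.
- **A condensed article need not rank its tests.** Which analyses are confirmatory may be settled in an analysis plan that is not shown. This stands in part: the missing ranking alone would be no finding. But the within-arm tests and the 0.05 rule over all p values are stated here, and a test that cannot answer the trial's question is a poor choice wherever the ranking is given.
- **A shared fall is not established.** Entry sets no minimum TNSS. Table 1 first records TNSS on day 0, apart from the eligibility check, although 2.4.1 lets the screening assessment serve as baseline. Antihistamines are prohibited during the study (2.3.2) but are not among the past-month exclusions (2.2.2), so someone stopping one could get worse. This stands: a fall in both arms is plausible but not certain.
- **The large percentages describe a different event.** A reader might take the upper figures, 50% to 96%, as the chance of a false efficacy claim. They are the chance that any one arm, placebo included, moves significantly from baseline. The misleading pattern of active significant and placebo not is much rarer and becomes less likely once the shared change is large. This stands, and the conclusion uses that smaller figure.

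**Conclusion.** The point holds as a reporting risk. Section 5.2 commits to inferential within-arm tests at every visit under the general 0.05 rule, and the primary outcome is not tied to the between-arm contrast. The between-arm test itself is unaffected.

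With 26 per arm, no treatment effect and a shared change of 0.2 to 0.75 SD, one arm's paired test is significant in about 17% to 96% of trials. The active arm alone is significant in about 4% to 25%, against 2.5% for a between-arm false positive favouring the drug. These figures rest on an assumed shared change, on normally distributed change scores, on independent arms and on all 26 per arm completing. If no shared change occurs, each paired test keeps its nominal 5%. Even then it does not address the comparison with placebo.

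The change is worth making: the tests add nothing to the trial's question and are easy to misread.

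**What to change.** In 5.2, remove the p values for within-arm comparisons and show the mean change from baseline per arm at each visit as description only. State that the between-arm difference in TNSS change at week 8, with its 95% CI, is the sole basis for the primary efficacy conclusion, and that secondary outcomes are likewise judged on the between-arm difference. Make the change before unblinding.

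The cost is a sentence or two. Data collection, randomisation and the power of the between-arm test are untouched, and nothing changes for subjects; section 9 reports 11 recruited by 18 July 2022, of the 58 planned. The one downside is that a conventional supplementary table loses its p values.

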### 2.3 Study intervention

#### 2.3.1 Study treatments

The eligible subjects will be randomly allocated to receive either “Yupingfeng Powder with variation” granules (15.55 g twice daily) or placebo granules (15.55 g twice daily) for 8 weeks. Variable dosages will be adopted according to the age of subjects. The daily dosage of “Yupingfeng Powder with variation” consists of the following herbal formula: *A. mongholicus* Bunge [Fabaceae] (Huang-Qi) 20 g, *A. macrocephala* Koidz. [Asteraceae] (Bai-Zhu) 10 g, *S. divaricata* (Turcz. ex Ledeb.) Schischk. [Apiaceae] (Fang-Feng) 6 g, *Magnolia biondii* Pamp. [Magnoliaceae] (Xin-Yi-Hua) 10 g, processed *Xanthium strumarium* L. [Asteraceae] (Chao-Cang-Er-Zi) 8 g, *Ganoderma lucidum* (Chi-Ling-Zhi) 12 g, *Platycodon grandiflorus* (Jacq.) A.DC. [Campanulaceae] (Ji-Geng) 10 g, processed *Drgonsbones* (Duan-Long-Gu) 15 g, processed *Ostreae concha* (Duan-Mu-Li) 15 g, *Terminalia chebula* Retz. [Combretaceae] (He-Zi) 8 g, *Glehnia littoralis* (A.Gray) F.Schmidt ex Miq. [Apiaceae] (Bei-Sha-Shen) 10 g, *Cordyceps sinesis* powder (Chong-Cao-Jun-Si-Fen) 3 g, *Dictamnus dasycarpus* Turcz. [Rutaceae] (Bai-Xian-Pi) 10 g. The study drug will be prepared using single granules, with the ratio of 1:3 for *A. macrocephala* Koidz. [Asteraceae] and 1:5 for the others according to the granules preparation method of the Nong’s Company Limited, i.e., 1 g granule = 3 g decoction piece and 1 g granule = 5 g decoction piece respectively, except for *Cordyceps sinesis* powder which is in the ratio of 1:1. The above granules are all extraction by water of the crude plants.

The granules are commercially available. The quality control and production of Nong’s Company Limited comply with the GMP standards of the PRC, Australia and the USP. All the herbal medicines comply with the standards of Chinese Pharmacopoeia. There is also laboratory for quality control with ISO 17025 certificate.

One daily dose of “Yupingfeng Powder with variation” granules will be equally sealed into two packs, which will be dissolved in hot water and administered while it is lukewarm. Participants will take two times daily, one pack in the morning and another in the evening after meal. Those subjects aged 5–12 will take half of the total dose, and those aged 13 or above will take normal adult dose.

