#### 2.4.3 Follow-up visit

CMP investigators with at least 3 years’ clinical experience will provide consultation under Chinese medicine theory, prescribe and dispense “Yupingfeng Powder with variation” granules or placebo in this trial. Subjects will return for follow-up at baseline, weeks 4 (±4 days) and 8 (±4 days), and followed by a post-treatment visit at weeks 12 and 16 (±4 days) (Table 1).

**TABLE 1 T1:** Study schedule.

Items	Screening	Treatment period			Post-treatment follow up	
	−14 to 0 days	Day 0 (baseline)	Week 4	Week 8	Week 12	Week 16
			(±4 days)	(±4 days)	(±4 days)	(±4 days)
Clinical assessment						
Informed consent	X					
Eligibility	X					
Medical consultation and assessment	X	X	X	X	X	X
Medical history	X					
Concomitant medication	X	X	X	X	X	X
Vital sign (BP/pulse)	X	X	X	X	X	X
AE/SAE assessment			X	X	X	X
Outcome assessment						
Total nasal symptom score (TNSS)		X	X	X	X	X
Visual analog scale (VAS)		X	X	X	X	X
Rhinoconjunctivitis Quality of Life Questionnaire (RQLQ) and Paediatric Allergic Disease Quality of Life Questionnaire (PADQLQ)		X	X	X	X	X
Serum level of IgE	X			X	X	
Serum levels of Cytokines (IL-10 and IL-17)		X		X	X	
Gut microbiota		X		X		
Laboratory assessment						
CBP with differentiation	X			X		
Renal and liver function test	X			X		
Intervention						
Administration of study drug		X	X	X		

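### The primary comparison uses the change in TNSS without naming baseline TNSS as a covariate; a prespecified ANCOVA would gain precision at no cost

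*Protocol article*

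**What the plan says.** Section 3.1 of the protocol article defines the primary outcome as "The change in the TNSS at week 8". The schedule in Table 1 (section 2.4.3) has TNSS measured on Day 0 and at weeks 4, 8, 12 and 16, so every randomised patient should have a baseline value.

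Section 5.2 has two sentences that bear on the group comparison:

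- Its first paragraph begins with the summary of baseline data and continues: "Differences of measurement data between the groups will be assessed using" a t-test, or a rank-based test if the data are not normal.
- Its second paragraph deals with data from the visits: "Comparisons between groups will be conducted by using an analysis of variance (ANOVA), with other confounding factors like multicenter character conducting the covariate analysis".

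Neither sentence mentions TNSS or says which analysis is primary. Centre is the only covariate named. Section 2.5 describes the envelopes as "one set for randomization at the site", with a second set kept for emergency unblinding, and no second centre appears in the article.

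On age, section 2.2.1 admits patients "Aged 5 or above", and section 2.3.1 states: "Those subjects aged 5–12 will take half of the total dose, and those aged 13 or above will take normal adult dose". Section 2.5 mentions no stratification by age.

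**The concern.** With two arms and no covariates, an ANOVA and a t-test are the same test. What distinguishes the stated ANOVA is therefore its covariates. The one that is named has no evident role in the design described, while the one most likely to help, the baseline value of the outcome itself, is not named.

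Subtracting baseline is not the same as adjusting for it. A change score fixes the slope of week-8 TNSS on baseline at 1. When the true slope is below 1, as regression to the mean implies, the change score over-corrects. This has two consequences:

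- the estimate has a larger variance than it needs;
- if the arms differ at baseline by chance, the estimated effect is pulled in a predictable direction.

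In a trial of 58 patients, 52 of them expected to be evaluable, precision is scarce, and this gain needs no extra data. An open covariate list for the primary comparison also leaves room to choose covariates after the results are known, unless another document closes it.

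**Working it through.** **Inputs from the article.** Two-sided 5% level (section 5.2). 80% power, 52 evaluable and 58 randomised, 29 per arm (section 5.1). Means 0.5 (SD 0.1) and 3.6 (SD 0.2) (section 5.1).

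**Assumptions.** The correlation r between baseline and week-8 TNSS is not given; 0.3, 0.5 and 0.7 are shown. The variance s² is taken as equal at both visits.

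**Step 1. The plan's own figure.** The dropout step reproduces: 52/0.9 = 57.8, so 58. The 52 itself does not follow from the quoted means and SDs. The pooled SD is √((0.1² + 0.2²)/2) = 0.158, so d = 3.1/0.158 = 19.6, for which the t-test needs only the minimum of 2 per arm. A total of 52 is what the two-sided t-test gives for d = 0.8 (26 per arm, power 80.7%). Exactly 80% at 26 per arm corresponds to d = 0.792. The power figures below use these back-solved values as a benchmark; the article states neither.

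**Step 2. Variance.**

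- Change score: 2s²(1 − r)
- ANCOVA: s²(1 − r²)
- Ratio: (1 − r²) / [2(1 − r)] = (1 + r)/2

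The ratio is below 1 for every r below 1, so the direction of the gain does not depend on the value chosen, apart from one degree of freedom for the covariate.

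**Step 3. Power at 26 per arm.** The standardised effect becomes d/√ratio.

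| r | Variance ratio | Reduction | Power, d = 0.792 (unadjusted 80%) | Power, d = 0.8, 1 df lost (unadjusted 80.7%) | Per arm for 80%, d = 0.8 |
|---|---|---|---|---|---|
| 0.3 | 0.65 | 35% | 93.5% | 93.9% | 17 |
| 0.5 | 0.75 | 25% | 89.9% | 90.4% | 20 |
| 0.7 | 0.85 | 15% | 85.9% | 86.6% | 22 |

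Equivalently, the 52 patients would carry the information of 52/ratio = 80, 69 or 61 patients analysed by change score.

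**Step 4. If the ANOVA were run on the week-8 score.** Section 5.2 speaks of data at each visit, so this reading is possible. The ratio is then 1 − r² = 0.91, 0.75 or 0.51. With d = 0.8 on that scale, power is 84.2, 90.4 or 97.7%. Adjustment gains here too.

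**Step 5. Chance imbalance.** At 26 per arm, the baseline difference between arms has standard error √(2/26) = 0.277 SD. Given an imbalance δ, the change-score estimate shifts by −(1 − r)δ. For an imbalance of one standard error the shift is 0.7 × 0.277 = 0.19, 0.5 × 0.277 = 0.14 or 0.3 × 0.277 = 0.08 SD. An effect of d = 0.8 on the change score equals 0.8√(2(1 − r)) SD, which is 0.95, 0.80 or 0.62 SD. The shift is therefore about 20, 17 or 13% of that effect.

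**Step 6. Age group.** The article does not say how much of the variance age explains. If it were 5 to 10% (an assumption), adjusting for age alone would raise power from 80.7% to 82.7–84.6%.

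**The case against.** The strongest objection is that nothing in section 5.2 is an error. Comparing change scores is valid under randomisation. The covariate sentence foresees adjustment and introduces centre only as an example, so baseline TNSS and age are unnamed but not excluded. A journal article may leave the full list to a statistical analysis plan. All of this stands, and it limits the point to a recommendation. It does not remove the efficiency gain over the method that the article does state.

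Several stronger readings are tempting, and the article does not support them:

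- **That the plan ignores baseline TNSS.** It does not, because the outcome is a change from baseline.
- **That the result would be biased.** Over randomisation it is not. The shift in Step 5 is conditional on a chance imbalance.
- **That the t-test and the ANOVA are two rival primary analyses.** The t-test sentence directly follows the one on baseline data and may refer only to baseline comparisons.
- **That baseline TNSS will vary widely.** No baseline SD is given, and eligibility already requires at least two nasal symptoms. The 0.277 SD applies to any variable at 26 per arm.
- **That age must be adjusted for because it sets the dose.** A dose that differs by age does not show that age predicts the change in TNSS.
- **That the trial is certainly single-centre.** The number of sites is never stated, and the singular may be generic.

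The power figures are also open to challenge. At the quoted means and SDs, power is close to 100% with or without adjustment. The equal-variance assumption may fail if scores fall towards zero on a bounded scale. The figures therefore illustrate the gain and do not predict it.

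**Conclusion.** The point holds as a free improvement. Section 5.2 names a group comparison for a change-score outcome and gives centre as its only example of a covariate. Baseline TNSS, which is already collected, is used only by subtraction. An ANCOVA with baseline TNSS would have 15 to 35% less variance for r between 0.7 and 0.3, with equal variances at both visits. If the unadjusted comparison has about 80% power with 26 per arm, adjustment raises it to about 86 to 93%. The direction is secure for any r below 1, apart from one degree of freedom. The size depends on r, which the article does not give, and the power figures also depend on an effect near 0.8 that is inferred from the sample size. A gain from adding age group is possible but cannot be quantified from the article.

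**What to change.** In section 5.2, or in the analysis plan before unblinding:

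1. Name one primary analysis: an ANCOVA of the week-8 change in TNSS on treatment and baseline TNSS, reported as the adjusted difference between arms with its 95% CI. Modelling the week-8 score in place of the change gives the same treatment estimate once baseline is in the model.
2. Use the same model, with the matching baseline value, for TNSS at the other visits and for the VAS and quality-of-life scores.
3. Close the covariate list. Age group (5–12 versus 13 or above) may be prespecified as a further covariate.
4. Keep a centre term only if more than one site randomises, and in that case state the sites. Otherwise delete it.
5. Say whether the t-test sentence is meant for baseline comparisons only.

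The cost is wording. Baseline TNSS and age are already collected, the sample size does not change, and section 9 reports only 11 participants recruited at the status date.
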